The Short-Form 36 (SF-36) is a validated multi-purpose, health survey with 36 questions, representing eight health domains that are combined into a physical and a mental component scale [38]. The Physical Component Summary (PCS) combines the health domains physical functioning (PF; 10 items), role limitations due to physical health (RP; 4 items), bodily pain (BP; 2 items), and general health perceptions (GH; 5 items). The Mental Component Summary (MCS) combines the health domains vitality, energy, or fatigue (VT; 4 items), social functioning (SF; 2 items), role limitations due to emotional problems (RE; 3 items), and general mental health (MH; 5 items). Scores ranging from 0 to 100 points are derived for each domain, with lower scores indicating poorer function. These scores will be converted to a norm-based score and compared with the norms for the general population of the United States (1998), in which each scale was scored to have the same average (50 points) and the same standard deviation (10 points).

The EuroQol-5D is a validated questionnaire for measuring health-related quality of life [39,40]. Its use is recommended for assessing quality of life in trauma patients, especially for economic assessments [41,42]. The EQ-5D descriptive system consists of five dimensions of health (mobility, self-care, usual activities, pain/discomfort and anxiety/depression). Scores are converted to a utility score ranging from zero to one, with lower scores indicating poorer quality of life. The EQ VAS records the respondents self-rated health status on a vertical (0–100) visual analog scale.

The cost-effectiveness analysis will be performed from a societal perspective and will include costs for health care and production losses. Patients will be asked to complete a custom-made questionnaire that contains detailed information on both items. Health care costs will include general practice care, medical specialist care, nursing care, physical therapy, hospitalization, medication, home care, and other costs directly associated with diagnosis, treatment, and rehabilitation.

In addition to the outcome variables mentioned above, the following data will be collected:

a) Intrinsic variables (baseline data): age, gender, American Society of Anesthesiologists’ ASA classification, tobacco consumption, alcohol consumption, comorbidities (including osteoporosis), dominant side, and medication use.

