b) Injury related variables: affected side, mechanism of injury, fracture classification according to the AO classification system, additional injuries, and admission duration.

c) Intervention-related variables: time between injury and start of treatment, days of collar and cuff, sling or plaster, time between injury and start of physical therapy, and number of physical therapy sessions.

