### Statistical analysis

Data will be analyzed using the Statistical Package for the Social Sciences (SPSS) version 21 or higher (SPSS, Chicago, Ill., USA) and will be reported following the STrengthening the Reporting of OBservational studies in Epidemiology (STROBE) guidelines. Normality of continuous data will be assessed by inspecting the frequency distributions (histograms), and homogeneity of variances will be tested using the Levene’s test.

Descriptive analysis will be performed to report baseline characteristics (intrinsic variables and injury-related variables) and outcome measures for both treatment groups.

For continuous data mean and SD (parametric data) or medians and percentiles (non-parametric data) will be calculated and reported. For categorical data, numbers and frequencies will be calculated and reported for both treatment groups.

Univariate analysis will be performed in order to test the difference in the primary and secondary outcome measures between the operative and the non-operative group. Continuous data such as the DASH score at the different time points (primary outcome) will be tested using a Student’s T-test (parametric data) or a Mann Whitney U-test (non-parametric data). Chi-square analysis will be used for statistical testing of categorical data such as the nonunion rate. A p-value <0.05 will be taken as threshold of statistical significance.

For the primary analysis, a mixed linear regression model will be developed in order to model the relation between different covariates and the DASH score over time. Intrinsic and fracture-related variables that display a p-value <0.5 in univariate analyses will be added as covariate. Similar models will be developed for the Constant, SF-36, and EQ-5D score. Subgroup analysis (*e.g.*, elderly versus <65 years) will be performed.

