For the secondary analysis we will develop a propensity score model as published before [43,44]. Characteristics including fracture type, age, gender, mechanism of injury, dominance, and activity levels will be included in this model; the resulting propensity score represents the chance of being operated. Next, the logit of the propensity score will be used in order to match each patient receiving operative treatment with one or more patients receiving non-operative treatment. The effect of operative treatment will be analyzed with linear or ordinal logistic mixed effects regression analysis taking the matched-pairs design into account. In the matched cohort, comparisons will be performed using a McNemar test (for categorical data), and a paired sample t test (parametric, continuous data) or a Wilcoxon signed rank test.

The economic evaluation will be performed from a societal perspective. Costs will be measured in accordance with Dutch guidelines for economic evaluations, using standard cost prices as published by Hakkaart-Van Rooijen et al. where possible [45]; effects will be discounted at a rate of 1.5% and costs at 4% per year [45]. The incremental cost-effectiveness ratio (ICER) of operative versus non-operative treatment will be expressed in a cost-utility ratio (*i.e.*, cost per QALY) using the EQ-5D utility score as effect measure. Uncertainty around this ratio will be presented using confidence ellipses on the cost-effectiveness plane and acceptability curves.

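### The primary mixed model chooses its confounders by a univariate p<0.5 screen, and the variable lists allow admission duration, known only after treatment is chosen, to enter as a baseline covariate

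*Protocol article*

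**What the plan says.** The protocol article, under Statistical analysis, names the main model: "For the primary analysis, a mixed linear regression model will be developed" for the DASH score over time. Its covariates come from a screen: "Intrinsic and fracture-related variables that display a p-value <0.5 in univariate analyses will be added as covariate". Similar models are planned for the Constant, SF-36 and EQ-5D scores.

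The candidates are listed under Outcome measures in three groups:
- Intrinsic: "a) Intrinsic variables (baseline data): age, gender, American Society of Anesthesiologists’ ASA classification, tobacco consumption, alcohol consumption, comorbidities (including osteoporosis), dominant side, and medication use".
- Injury related: "b) Injury related variables: affected side, mechanism of injury, fracture classification according to the AO classification system, additional injuries, and admission duration".
- Intervention-related, which begins: "c) Intervention-related variables: time between injury and start of treatment, days of collar and cuff, sling or plaster". Admission duration is not in this group.

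The descriptive analysis is to "report baseline characteristics (intrinsic variables and injury-related variables"), so the second group, with admission duration in it, counts as baseline.

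The propensity-score analysis, which is secondary, names its covariates: "Characteristics including fracture type, age, gender, mechanism of injury, dominance, and activity levels will be included in this model". Admission duration is not among those named.

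**The concern.** In a surgeon-allocated comparison the covariate set is the primary model's only protection against confounding. Here a p-value chooses it, so it can differ between outcomes and from the propensity model.

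The more serious part is what the screen may let in. Under Recruitment and consent, patients are enrolled in the emergency department or at the first outpatient visit. Under Study population, surgery may follow up to 14 days after presentation. The length of an admission that includes the operation cannot be known before treatment is chosen. Conditioning on a variable that treatment affects removes any part of the effect that runs through it. If that variable also shares unmeasured causes with the outcome, conditioning creates a spurious association between treatment and outcome. The estimate at stake is the study's main answer, and the planned difference is only 6 DASH points.

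**Working it through.** **1. The plan's own figure.** From Sample size calculation: means 16 and 10, SDs 16 and 10, two-sided alpha 0.05, power 0.80.

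n per group = (1.960 + 0.842)² × (16² + 10²) / 6² = 7.849 × 356 / 36 = 77.6, so 78, as stated. The stated 95 follows from 78 × 1.1 × 1.1 = 94.4. Neither figure depends on the covariate rule.

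**2. Inputs for the illustration.**
- From the document: a true effect of -6; within-arm DASH SD √(356/2) = 13.34; 400 patients less 10% mortality and 10% loss to follow-up, giving 320, or 160 per group. The unadjusted SE is 13.34 × √(2/160) = 1.49.
- Assumed, because the document has no length-of-stay data: surgery adds d = 2.5 days; stay has within-arm SD s; an unmeasured frailty factor correlates ρ with stay within arm and adds b DASH points per SD; stay has no effect of its own on DASH.

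**3. Formulas.** Within arm, the slope of DASH on stay is bρ/s. Therefore:
- adjusted effect = -6 - bρ(d/s)
- SE multiplier from collinearity in equal groups = √(1 + (d/s)²/4), before any small gain from lower residual variance.

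| s (days) | ρ | b = 2 | b = 4 | b = 6 | SE multiplier |
|---|---|---|---|---|---|
| 5 | 0.3 | -6.3 | -6.6 | -6.9 | 1.03 |
| 5 | 0.6 | -6.6 | -7.2 | -7.8 | 1.03 |
| 2.5 | 0.3 | -6.6 | -7.2 | -7.8 | 1.12 |
| 1.25 | 0.6 | -8.4 | -10.8 | -13.2 | 1.41 |

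For example, the bottom right cell is -6 - 6 × 0.6 × (2.5/1.25) = -13.2. With b = 0 every cell is -6.0: the SE cost remains but there is no bias. With d = 0 there is also no bias.

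A separate simulation (400 patients, 1,000 runs per setting) used other assumptions: within-arm correlation of stay with frailty 0.71, frailty worth 3 or 5 points per SD, and a shift in stay of 0.35 to 1.41 within-arm SDs. It gave adjusted estimates from -6.8 to -11.0.

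**4. Would admission duration pass the screen?** The document does not say whether the univariate test is against DASH or against treatment. Against DASH, the marginal covariance is d × (-6)/4 + bρs. The two terms have opposite signs and can cancel. In the simulation the pass rate with a shared cause and a shift in stay ran from 49% to 99.9%; a pure noise variable passes 50% of the time. At the 49% setting the mean estimate was -5.9 unadjusted, -9.0 adjusted, and -7.4 under the rule. Its SD across runs was 1.27, 1.58 and 2.00 respectively, so selection itself adds variability.

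**5. Does the screen lose real confounders?** By Fisher's z at n = 320, a covariate correlated 0.10 with DASH has z = 0.1003 × √317 = 1.786. It is dropped with probability Φ(0.674 - 1.786) - Φ(-0.674 - 1.786) = 0.133 - 0.007 = 0.13. The same formula gives 0.36 at correlation 0.05 and 0.02 at 0.15. If such a covariate differs between arms by an assumed 0.3 SD, omitting one with correlation 0.10 shifts the effect by 0.10 × 13.34 × 0.3 = 0.4 points, against 6.

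**The case against.** A reader might infer that the primary effect is over-adjusted as planned. The text does not support that. The covariate sentence says fracture-related and the descriptive sentence says injury-related. On a narrow reading, such as AO class and affected side, admission duration never enters. The document also does not say that surgery determines stay, and stay may partly reflect injury severity. Bias needs the wide reading, a pass at p<0.5, an effect of surgery on stay, and mediation or a shared cause with DASH.

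A reader might also take the upper end of the range as the expected size. It holds only if 2.5 days equals two within-arm SDs of stay and the frailty correlation is near 0.6. With no upper age limit, so tight a spread is not supported. The illustration also adjusts for nothing else, whereas ASA, age and comorbidities are in the pool and would absorb part of the shared cause.

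Finally, 0.5 may be a deliberately inclusive screen or a misprint for 0.05; the document does not settle which. As printed it loses few real confounders, and the propensity analysis is a planned check with named covariates, although its list is open-ended.

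These objections limit the certainty and the size. They do not remove the point. The screen is printed as the rule for the primary analysis, so it is not a detail left to an analysis plan. Labelling admission duration as baseline is wrong on either reading, and on the narrow reading the pool of candidates is undefined.

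**Conclusion.** The point holds in conditional form. The plan leaves the primary confounder set to a univariate p-value and allows a variable known only after treatment choice to enter. If surgery lengthens stay and stay mediates the effect or shares unmeasured causes with DASH, the main estimate is biased. For a true -6 and a 2.5-day shift, the adjusted value runs from about -6.3 (SD of stay 5 days, correlation 0.3, 2 points per SD of frailty) to about -13 (1.25 days, 0.6, 6 points). The collinearity cost is 3% to 41% on the SE. A looser spread and weaker correlation (SD 2.5 to 5 days, correlation 0.3) give -6.3 to -7.8. In these scenarios the bias favours surgery, the direction of the study's hypothesis, but the direction depends on the assumed signs. The loss of true confounders is a minor matter. This should be fixed before analysis; confidence in the size is moderate, because every length-of-stay input is assumed.

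**What to change.** Take admission duration out of the injury-related baseline variables and report it as resource use.

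Replace the p<0.5 screen with a pre-specified set of pre-treatment covariates forced into the primary model: fracture type, age, gender, mechanism of injury, dominance, ASA class, smoking, and comorbidities including osteoporosis. Add activity level if it is collected; it is in the propensity list but in none of the three variable lists, so its collection should be confirmed. Use one term for the injury-related group throughout.

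The cost is analysis wording only. All items named, apart from activity level, are already listed for collection, and the stated 78 and 95 per group and the total of 400 do not change.

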**Methods/design:**

The design of the study will be a multicenter prospective observational study of 400 patients who have sustained a humeral shaft fracture, AO type 12A or 12B. Treatment decision (*i.e.*, operative or non-operative) will be left to the discretion of the treating surgeon. Critical elements of treatment will be registered and outcome will be monitored at regular intervals over the subsequent 12 months. The primary outcome measure is the Disabilities of the Arm, Shoulder, and Hand score. Secondary outcome measures are the Constant score, pain level at both sides, range of motion of the elbow and shoulder joint at both sides, radiographic healing, rate of complications and (secondary) interventions, health-related quality of life (Short-Form 36 and EuroQol-5D), time to resumption of ADL/work, and cost-effectiveness. Data will be analyzed using univariate and multivariable analyses (including mixed effects regression analysis). The cost-effectiveness analysis will be performed from a societal perspective.

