## Methods/design

### Study design

The HUMMER trial will follow a multicenter, prospective observational trial design. Approximately 30 hospitals in The Netherlands will participate.

The decision to provide operative or non-operative treatment will be left to the discretion of the attending physician. We chose an observational design because a randomized controlled trial (RCT) would currently not be feasible. Many surgeons prefer not to participate in trials that involve randomization [21] and we know from experience that patients easily refuse to be randomized between operative and non-operative treatment. Inclusion problems were the main reason for failure of a previous RCT with the same research question as this study [20]. Well-designed and adequately reported observational studies are good alternatives to RCTs [22,23]. Preference of observational studies over RCTs in orthopedic trauma has been acknowledged [24,25]. They lead to similar outcomes without the limitations of randomization which may in practice decrease the validity of the outcomes [26,27]. These designs are increasingly used and accepted in surgical studies [28]. In order to answer our research question, we will make adjustments in the statistical analysis by using the propensity matching score method [29-32].

The trial is registered at the Netherlands Trial Register (NTR3617).

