### Intervention

The decision on treatment will be left to the discretion of the attending surgeon. The choice will be between operative and non-operative treatment. Also, the rehabilitation after treatment will not be standardized, but will be provided as in real life. Although this may create some heterogeneity across groups, it will improve the generalizability of the study results.

If a surgeon decides to operate the patient, the choice between plate osteosynthesis or intramedullary nailing will be left to the treating surgeon. No restrictions will be applied to the approach for reduction and fixation of the fracture, *e.g.*, open or closed, antegrade or retrograde. The type and brand of the materials as well as the use of cerclage wires and other elements of the surgery will be left to the surgeon, local availability and expertise. Critical elements of the operative treatment will be recorded (*e.g.*, type of implant, identification of the radial nerve, surgical approach, operative delay, duration of surgery) and the effect on outcome will be assessed.

In order to maximize generalizability, the type of non-operative treatment will also be left to the attending surgeon. Usually it consists of a splint, plaster, collar and cuff or hanging cast for 1–2 weeks, followed by a Sarmiento brace for 4–6 weeks. Critical elements of this treatment will be recorded and the effect on outcome will be assessed.

Due to a lack of evidence favoring a particular approach, the physical therapy and rehabilitation program will be recorded but not standardized. This will improve generalization of the study results.

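### The covariate rule for the primary model admits only patient and fracture variables, so differences between about 30 hospitals in who is operated and how patients fare are not adjusted for

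*Protocol article*

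**What the plan says.** The trial is a "multicenter prospective observational study of 400 patients" (Abstract), and "Approximately 30 hospitals in The Netherlands will participate" (Study design). The Intervention section states "The decision on treatment will be left to the discretion of the attending surgeon". Implants, cerclage and "other elements of the surgery will be left to the surgeon, local availability and expertise"; likewise "the physical therapy and rehabilitation program will be recorded but not standardized".

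The Statistical analysis section makes a mixed linear regression of DASH over time the primary analysis. Its covariates are chosen by one rule: "Intrinsic and fracture-related variables that display a p-value <0.5 in univariate analyses will be added as covariate". Similar models are planned for Constant, SF-36 and EQ-5D. The Outcome measures section lists the two classes of variable. Intrinsic variables are age, gender, ASA class, smoking, alcohol, comorbidity, dominant side and medication. Injury-related variables are side, mechanism, AO class, other injuries and length of admission. Neither list contains hospital or surgeon.

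For the secondary, propensity-based analysis: "Characteristics including fracture type, age, gender, mechanism of injury, dominance, and activity levels will be included in this model". The matched analysis accounts for the matched pairs and names no other grouping. The random effects of the primary model are not stated.

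**The concern.** The comparison is not randomised, and the Study design section relies on statistical adjustment to answer the research question. The set of adjustment variables is therefore the main safeguard.

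The protocol's own account points to the provider as a driver of treatment. The Background says that surgeons' experience helps to guide the choice and that some surgeons operate where others do not. It also reports an operation rate near 50% whatever the fracture subclass, with no obvious differences in patient or fracture characteristics. The provider can also plausibly affect outcome, through expertise, materials and aftercare. A factor linked to both treatment and outcome is a confounder, and a rule confined to patient and fracture variables does not reach it.

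At stake is a treatment estimate that partly reflects which hospitals operate more. The direction is unknown. If hospitals that operate more also have lower mean DASH for other reasons, surgery looks better than it is; if higher, worse.

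**Working it through.** **1. The plan's own figure.** The Sample size calculation gives means of 16 and 10, SDs of 16 and 10, two-sided alpha 0.05 and power 0.80.

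- Common SD = √((16² + 10²)/2) = √178 = 13.34.
- n per group = 2 × (1.960 + 0.842)² × 178 / 6² = 77.6, rounded up to 78.

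The stated 78 is reproduced. The formula treats patients as independent.

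**2. Inputs that the documents do not give (assumed).**

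- Outcome ICC, the share of DASH variance lying between hospitals: 0.05 to 0.10, with 0.01 as a low case.
- Treatment ICC, the share of variance in operated/not operated lying between hospitals: 0 (equal rates), 0.1 or 0.3.
- r, the correlation between a hospital's operation tendency and its mean DASH: 0, 0.3 or 0.5 in absolute value.
- Mean hospital size m = 400/30 = 13.3, and half of the patients operated.

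**3. Standard error.** Treatment is chosen patient by patient, so the design effect is 1 + (m − 1) × outcome ICC × treatment ICC. The last two columns show the effect of ignoring hospital.

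| Outcome ICC | Treatment ICC | Design effect | True SE / reported SE | Two-sided type I error |
|---|---|---|---|---|
| 0.05 or 0.10 | 0 | 1.00 | 1.00 | 0.050 |
| 0.05 | 0.1 | 1.06 | 1.03 | 0.057 |
| 0.05 | 0.3 | 1.19 | 1.09 | 0.072 |
| 0.10 | 0.1 | 1.12 | 1.06 | 0.064 |
| 0.10 | 0.3 | 1.37 | 1.17 | 0.094 |

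Example: 1 + 12.33 × 0.10 × 0.3 = 1.37, and √1.37 = 1.17. With equal operation rates there is no problem, whatever the outcome ICC.

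**4. Bias.** The bias of a contrast that ignores hospital is the covariance of hospital effect and operation probability, divided by the treatment variance of 0.25:

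bias = r × √(outcome ICC) × 13.34 × √(0.25 × treatment ICC) / 0.25.

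| Outcome ICC | Treatment ICC | r = 0.3 | r = 0.5 |
|---|---|---|---|
| 0.01 | 0.1 | 0.25 | 0.42 |
| 0.01 | 0.3 | 0.44 | 0.73 |
| 0.05 | 0.1 | 0.57 | 0.94 |
| 0.05 | 0.3 | 0.98 | 1.63 |
| 0.10 | 0.1 | 0.80 | 1.33 |
| 0.10 | 0.3 | 1.39 | 2.31 |

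For outcome ICC 0.05 to 0.10 the range is 0.57 to 2.31 DASH points. Against the planned 6 points that is 0.57/6 = 9% to 2.31/6 = 39%.

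**5. Check by simulation.** One DASH time point, 400 patients, 30 hospitals, no true effect, no patient covariates, 2,000 runs per setting, outcome ICC 0.05 and 0.10.

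- Equal rates: reported SE / true SE was 1.02 and 0.99; type I error 0.042 and 0.051.
- Rates differ, r = 0: ratio 0.99 to 0.86; type I error 0.055 to 0.094.
- Rates differ, r = 0.5: bias 0.9 to 2.2 points, in line with step 4.
- With hospital fixed effects, bias was at most 0.06 points in every setting, and type I error was about 0.04 to 0.06.

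**6. A random intercept alone is not enough.** In a random-intercept model the between-hospital comparison keeps a relative weight of (1 − ICC)/(1 − ICC + m × ICC). That is 0.95/(0.95 + 0.667) = 0.59 at ICC 0.05 and 0.90/(0.90 + 1.333) = 0.40 at ICC 0.10. Much of the confounded comparison therefore stays in the estimate. Adding the hospital's proportion operated, or using fixed effects, makes the treatment contrast a within-hospital one.

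**The case against.** The strongest objection is that this is a condensed article. A mixed model has a random part, here unstated, and a hospital intercept could sit in it. The propensity list opens with the word including, so it is not closed. A fuller protocol or analysis plan may settle both. That stands: for the random effects and the propensity model one can say only that no hospital adjustment is named. It does not remove the point, because the rule for fixed covariates is stated, hospital falls outside it, and a random intercept alone would take out only part of the bias.

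Second, the attending surgeon chooses, not the hospital, and the operation rates given are by fracture subclass. This also stands. Variation between hospitals is an inference, supported mainly by the reliance on local availability and expertise.

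Third, the bias is driven by an assumed correlation, and the simulation had no patient covariates. Age, ASA class, comorbidity and AO class could absorb part of any difference in case mix. Rehabilitation also follows the treatment choice, so some of it belongs to the strategy being compared. The figures are therefore scenarios, not predictions.

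A reader might also infer three stronger things that the documents do not support:

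- That correlation within hospitals by itself makes intervals too narrow. It does so only if operation rates also differ between hospitals. Design effects for a fully clustered treatment do not apply, because patients are not treated by hospital policy.
- That very high false-positive rates are to be expected. These appear only when strong confounding is put in as an assumption.
- That matching must be within hospital. With about 13 patients per hospital many operated patients could lack a match, so this is a trade-off and not a requirement.

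**Conclusion.** The point holds in limited form. As written, the covariate rule of the primary model leaves hospital unadjusted in a non-randomised comparison where the choice of treatment, the technique and the aftercare are local. Bias is the main risk: about 0.6 to 2.3 DASH points against a 6-point target. This assumes an outcome ICC of 0.05 to 0.10, a treatment ICC of 0.1 to 0.3 and a correlation of 0.3 to 0.5. It is smaller at lower ICCs, and zero if operation tendency and hospital outcome are unrelated.

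The effect on standard errors is secondary and conditional. The true standard error is about 3% to 17% above the reported one if operation rates differ between hospitals, and about equal to it if they do not. None of this shows that the trial's estimate will be biased. It shows that a cheap protection is missing from the stated rule, and the plan should add it.

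**What to change.** Extend the covariate rule in the Statistical analysis section so that hospital enters the mixed models for DASH, Constant, SF-36 and EQ-5D regardless of any univariate p-value. Use either a random intercept for hospital plus the hospital's proportion operated as a covariate, or hospital fixed effects. Report the operation rate by hospital, so that readers can see how much the rates differ. For the propensity analysis, state whether hospital is in the model and whether matching is within or across hospitals.

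The change needs no new data, since the treating hospital is known for every patient. The cost is precision. In the simulated settings with differing rates, the fixed-effects standard error was 4% (1.386 against 1.335) to 21% (1.618 against 1.339) above the one that ignores hospital; part of that corrects a value that was too small. Hospitals that treat everyone one way add little to the within-hospital contrast.

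The planned size can bear this. Take the largest of these standard errors, 1.618 with 400 patients, and 160 evaluable per group (200 × 0.8). It becomes about 1.618 × √(400/320) = 1.81. Then 6/1.81 = 3.32, and power is Φ(3.32 − 1.96) = Φ(1.36), roughly 91%.

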### Sample size calculation

Calculation of the required sample size for the primary analysis is based on the assumption that the mean DASH in the non-operative group will be 16, with a Standard Deviation (SD) of 16 [8]. We expect less disability (*i.e.*, lower DASH score) at three months in the operative group; the expected DASH score in the operative group will be 10 (SD 10) [8]. A two-sided test with an α level of 0.05 and a β level of 0.2 requires 78 patients in every group. In order to account for loss of patients due to mortality (10%) and loss-to-FU (10% anticipated based upon previous studies by the research team), a sample size of 95 patients per group is needed.

Results of a retrospective study assessing clinical outcome of humeral shaft fractures, showed that 45-55% of all AO-subclasses were treated operatively [18]. In order to assess whether functional outcome scores differ between the fracture subtypes, a minimum of 2x20 patients per fracture subtype is sufficient. In order to achieve that, we need to include until at least 200 patients in both the operative groups and the non-operative group.

For the secondary analysis, some patients may be lost during the propensity score matching. Although we do not have a-priori data to determine how many patients will be lost, the 400 targeted patients will be more than sufficient.

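### The secondary propensity analysis allows several controls per operated patient, but its simple matched comparisons use tests built for one-to-one pairs

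*Protocol article*

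**What the plan says.** All of this stands in the protocol article, mostly under Statistical analysis.

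- **Rank.** The propensity work is secondary: "For the secondary analysis we will develop a propensity score model as published before". The primary analysis is a different one, on the unmatched cohort: "For the primary analysis, a mixed linear regression model will be developed".
- **Matching.** On the logit of the propensity score, the plan is to "match each patient receiving operative treatment with one or more patients receiving non-operative treatment". The ratio is left open.
- **Treatment effect after matching.** It will be "analyzed with linear or ordinal logistic mixed effects regression analysis taking the matched-pairs design into account".
- **Simple comparisons after matching.** "comparisons will be performed using a McNemar test (for categorical data), and a paired sample t test" for parametric continuous data, with the Wilcoxon signed-rank test as the alternative.
- **Threshold.** "A p-value <0.05 will be taken as threshold of statistical significance".
- **Group sizes.** Sample size calculation plans at least 200 patients per treatment group. It cites a retrospective study which "showed that 45-55% of all AO-subclasses were treated operatively", and it accepts that matching may lose some patients.

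**The concern.** The matching sentence permits sets with one operated patient and two or more controls. The comparison sentence names three tests whose usual input is a single pair. McNemar's table has no cell for a second control, and the paired t and signed-rank tests work on one difference per pair. For a larger set the analyst must repeat the operated patient, discard controls or average them. These choices give different p-values, and the article selects none of them.

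Repeating the operated patient is the harmful choice. The resulting pairs share a patient and are not independent, so the standard error comes out too small.

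What is at stake is the matched comparison of simple outcomes. McNemar is the only simple matched test named for categorical data, which would include non-union, complications and secondary interventions. Surgeons choose the treatment, and Study design presents propensity matching as the adjustment that lets the research question be answered. Readers will therefore give these p-values some weight.

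**Working it through.** **The plan's own figure.** The article gives no pair count or power for the matched analysis. Its only sample size figure is for the unmatched comparison, and it reproduces: (16² + 10²)(1.960 + 0.842)²/6² = 77.6, rounded up to 78 per group. It does not bear on this point.

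**Inputs from Sample size calculation.** 45-55% operated; 400 patients in total; at least 200 per group.

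**Assumptions not in the documents.** Larger sets are entered as separate pairs; variances are equal in the two groups; controls are not reused; every operated patient is matched and all controls are used; no set has more than two controls unless stated.

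**Formula.** Let set i have mᵢ controls and let N = Σmᵢ be the number of pseudo-pairs.

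- True variance of the mean difference: σ²(Σmᵢ² + N)/N²
- Variance that a paired t-test assumes: 2σ²/N
- Ratio of true to assumed standard error: k = √[(Σmᵢ² + N)/(2N)]
- Actual two-sided error rate: 2[1 − Φ(1.96/k)]

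A shared set effect cancels in each difference, so within-set correlation does not change k.

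**Results**

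| Scenario | Sets | N | Σmᵢ² | k | Actual alpha |
|---|---|---|---|---|---|
| 200/200, all 1:1 | 200 | 200 | 200 | 1.000 | 5.0% |
| 180/220 (45% of 400 operated) | 140 at 1:1, 40 at 1:2 | 220 | 300 | √(520/440) = 1.087 | 7.1% |
| 200/244 (recruit until both groups reach 200 at 45%: 200/0.45 ≈ 444) | 156 at 1:1, 44 at 1:2 | 244 | 332 | √(576/488) = 1.086 | 7.1% |
| All sets 1:2 | – | – | – | √(6/4) = 1.225 | 11.0% |
| All sets 1:3 | – | – | – | √(12/6) = 1.414 | 16.6% |

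**Are the last two rows reachable?** Giving 200 operated patients two or three controls each takes 400 or 600 controls, against about 200 planned. Without reuse, 200 controls serve only 100 operated patients at 1:2 or 66 at 1:3. These rows therefore require reused controls or many unmatched operated patients.

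**Simulation check.** 10,000 runs per scenario, no treatment effect, within-set correlation 0 and 0.3, and an assumed 15% event rate for McNemar:

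- Exact 1:1 pairs: 5.0-5.2% for all three tests.
- 180/220 expanded into pairs: 6.9-7.2% for all three tests.
- All 1:2: about 11%. All 1:3: 16-17%.
- Paired t-test on the operated value minus the mean of the set's controls: 4.6-5.4% across all scenarios.

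**Sensitivity of the 7%.**

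- With the protocol's planning SDs (10 operated, 16 non-operated), 180/220 gives k = √[(300·100 + 220·256)/(220·356)] = 1.050, an error rate of about 6.2%.
- If the 40 spare controls formed 20 sets of 1:3 instead, with equal variances, Σmᵢ² = 160 + 180 = 340 and k = √(560/440) = 1.128, about 8.2%.

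**The case against.** The strongest reply is that the analysis that matters is already sound. The sentence between the matching rule and the paired tests assigns the treatment effect to mixed-effects regression, and a matched-set effect in that model handles sets of any size. This stands. A reader might infer that all the matched p-values are invalid; the article does not support that, because only the three simple tests are affected.

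A second reply is that nothing says operated patients will be repeated. This also stands. For larger sets the tests are undefined rather than shown to be wrong: they are valid if every set turns out 1:1, which the wording allows, and a paired t-test on set-mean differences is valid too.

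A third concerns reuse. A reader might infer that near-equal groups force controls to be used more than once. They do not: at 200 and 200, one control each satisfies the rule. The article nowhere mentions matching with replacement, and it expects some patients to be lost in matching.

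A fourth is that this is a condensed article which builds the propensity model on published work, so the caliper, replacement rule and final ratio may be set out elsewhere. Their absence is not counted here. What remains is that two stated sentences do not fit each other. Overall balance does not remove this, since controls can outnumber operated patients locally where surgery is unlikely.

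**Conclusion.** The point holds in limited form. The stated matching rule and the stated simple tests are incompatible as soon as any set has more than one control. This affects the McNemar, paired t and signed-rank comparisons in the secondary propensity analysis. It does not affect the mixed-effects estimate of the treatment effect or the primary DASH model.

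If the extra controls were entered as separate pairs, the actual error rate would be about 7% instead of 5% at the 45% edge of the expected operated share. That rests on the assumptions listed in the working and moves modestly with them. With all sets at 1:1 there is no inflation. The 11% and 17% figures are not a fair description of this plan, because they need reused controls or many unmatched operated patients.

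The sponsor should fix this, but it is not critical to the trial's main conclusion.

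**What to change.** Before matching, choose one of two and state it in a sentence.

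- **(a)** Specify 1:1 matching without replacement, keep the three paired tests, and report how many operated patients stay unmatched. This suits near-equal groups. The cost is that some patients are dropped.
- **(b)** Keep 1:m matching and replace the three tests with set-aware methods: a mixed model with a matched-set effect for continuous outcomes and conditional logistic regression for binary outcomes. State whether controls are reused and, if so, use standard errors that allow for it. The cost is giving up the simpler tests.

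Either choice needs no extra patients or data, and it removes a choice of ratio and test that would otherwise be made after the data are seen.
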